### Participants and recruitment

Participants scheduled to undergo allo-SCT at the Alfred Hospital, Melbourne, Victoria will undergo initial eligibility screening by their nurse transplant coordinator. If identified as interested and eligible based on the criteria outlined in Table 1, the nurse transplant coordinator will provide the participant’s contact details to the ALLO-Active study coordinator. Following further discussion of the purpose of the study and participation requirements via telephone with the ALLO-Active study coordinator, the participant will be provided a participant information and consent form.

**Table 1 Tab1:** Participant eligibility criteria

Inclusion Criteria	Exclusion Criteria
- Age ≥ 18 years	- Unable to communicate or read in English
- Scheduled for allo-SCT	- Contraindications to 3 T MRI (e.g., pacemaker or implanted metallic device)
- Able to exercise at time of enrolment	

After informed consent is acquired, participant demographics, health status, current medications, and cardiovascular risk profile (including family history of CVD, presence of cardiovascular risk factors or overt cardiovascular disease, smoking status, alcohol consumption and menstrual reproductive history) will be documented by questionnaire at baseline. Additional relevant medical history will be extracted from medical records and will include information related to each participants hematological cancer diagnosis, prior anti-cancer treatment history, stem cell transplant conditioning regimen (protocol and dosage [intensity and agents]) and donor (relation, graft source, HLA matching).

### Intervention

This is an individualised, multi-faceted intervention designed to increase aerobic and resistance exercise and reduce prolonged sedentary behaviour with the global aim of attenuating the negative impact of allo-SCT on cardiovascular function. The two intervention components will be delivered in parallel, over two distinct phases: Phase 1—commenced upon inpatient admission for allo-SCT and continued for the duration of inpatient care (~ 4 weeks); and Phase 2—commenced immediately post-discharge from inpatient care and continued for 12 weeks. Participants will be provided with a wrist worn smartwatch (Fitbit Ionic or Fitbit Versa 2, Fitbit, Inc., San Francisco, CA, USA) that will be worn at all times to facilitate and monitor adherence to the intervention. Each device will be connected to a cloud-based data aggregation platform (Fitabase Small Steps Labs, LLC, San Diego, CA) wherein 24/7 heart rate, step count, and intensity (time spent in light, moderate and high intensity activity) data will be captured in real-time. An overview of the exercise intervention can be found in Table 2.

**Table 2 Tab2:** Outline of the ALLO-Active multi-faceted Ex + SED program

Phase	Weeks	Session Type	Frequency (per/week)	Duration/Dose	Intensity
1—Inpatient	1, 3–4	Continuous Aerobic & Resistance	2	*AT:* 20 min *RT:* 4–6 ex, 1 set × 15 reps	*AT:* 60% VO_2_peak, 12–14 RPE *RT:* 14–16 RPE
		Interval & Resistance	1	*AT:* 4 × 2 min on, 3 min off *RT:* 4–6 ex, 1 set × 15 reps	*AT:* 80% VO_2_peak, 85–95% HRpeak, and/or ≥ 17 RPE *RT:* 14–16 RPE
	2	Continuous Aerobic & Resistance	3	*AT:* 20 min *RT:* 4-6 ex, 1 set × 15 reps	*AT:* 60% VO_2_peak, 12–14 RPE *RT:* 14–16 RPE
	1–4	Sedentary Behaviour Breaks	7	10 x ≥ 3 min per day, completed hourly	Light (normal breathing rate – can sing or talk)
2—Outpatient	1–2	Continuous Aerobic & Resistance	1	*AT:* 20 min (wk1), 21 min (wk2) *RT:* 6–8 ex, 2 sets × 10–15 reps	*AT:* 60% VO_2_peak, 12–14 RPE *RT:* 14–16 RPE
		Interval & Resistance	1	*AT:* 4 × 2 min on, 3 min off *RT:* 6–8 ex, 2 sets × 10–15 reps	*AT:* 80% VO_2_peak, 85–95% HRpeak, and/or ≥ 17 RPE *RT:* 14–16 RPE
		Continuous Aerobic (Home)	1	*AT:* 20 min (wk1), 21 min (wk2)	*AT:* 60% VO_2_peak, 12–14 RPE
	3–4	Continuous Aerobic & Resistance	1	*AT:* 22 min (wk3), 23 min (wk4) *RT:* 6–8 ex, 2 sets × 10–15 reps	*AT:* 60% VO_2_peak, 12–14 RPE *RT:* 14–16 RPE
		Interval & Resistance	1	*AT:* 6 × 2 min on, 3 min off *RT:* 6–8 ex, 2 sets × 10–15 reps	*AT:* 80% VO_2_peak, 85–95% HRpeak, and/or ≥ 17 RPE *RT:* 14–16 RPE
		Continuous Aerobic (Home)	1	*AT:* 22 min (wk3), 23 min (wk4)	*AT:* 60% VO_2_peak, 12–14 RPE
	5–6	Continuous Aerobic & Resistance	1	*AT:* 24 min (wk5), 25 min (wk6) *RT:* 6–8 ex, 2 sets × 10–15 reps	*AT:* 60% VO_2_peak, 12–14 RPE *RT:* 14–16 RPE
		Interval & Resistance	1	*AT:* 4 × 3 min on, 3 min off *RT:* 6–8 ex, 2 sets × 10–15 reps	*AT:* 80% VO_2_peak, 85–95% HRpeak, and/or ≥ 17 RPE *RT:* 14–16 RPE
		Continuous Aerobic (Home)	1	*AT:* 24 min (wk5), 25 min (wk6)	*AT:* 60% VO_2_peak, 12–14 RPE
	7–8	Continuous Aerobic & Resistance	1	*AT:* 25 min (wk7), 26 min (wk8) *RT:* 6–8 ex, 2 sets × 10–15 reps	*AT:* 60% VO_2_peak, 12–14 RPE *RT:* 14–16 RPE
		Interval & Resistance	1	*AT:* 4 × 3 min on, 2 min off *RT:* 6–8 ex, 2 sets × 10–15 reps	*AT:* 80% VO_2_peak, 85–95% HRpeak, and/or ≥ 17 RPE *RT:* 14–16 RPE
		Continuous Aerobic (Home)	1	*AT:* 25 min (wk7), 26 min (wk8)	*AT:* 60% VO_2_peak, 12–14 RPE
	9–10	Continuous Aerobic & Resistance	1	*AT:* 27 min (wk9), 28 min (wk10) *RT:* 6–8 ex, 2 sets × 10–15 reps	*AT:* 60% VO_2_peak, 12–14 RPE *RT:* 14–16 RPE
		Interval & Resistance	1	*AT:* 5 × 3 min on, 2 min off *RT:* 6–8 ex, 2 sets × 10–15 reps	*AT:* 80% VO_2_peak, 85–95% HRpeak, and/or ≥ 17 RPE *RT:* 14–16 RPE
		Continuous Aerobic (Home)	1	*AT:* 27 min (wk9), 28 min (wk10)	*AT:* 60% VO_2_peak, 12–14 RPE
	11–12	Continuous Aerobic & Resistance	1	*AT:* 29 min (wk11), 30 min (wk12) *RT:* 6–8 ex, 2 sets × 10–15 reps	*AT:* 60% VO_2_peak, 12–14 RPE *RT:* 14–16 RPE
		Interval & Resistance	1	*AT:* 6 × 3 min on, 2 min off *RT:* 6–8 ex, 2 sets × 10–15 reps	*AT:* 80% VO_2_peak, 85–95% HRpeak, and/or ≥ 17 RPE *RT:* 14–16 RPE
		Continuous Aerobic (Home)	1	*AT:* 29 min (wk11), 30 min (wk12)	*AT:* 60% VO_2_peak, 12–14 RPE
	1–12	Sedentary Behaviour Breaks	7	10 x ≥ 3 min per day, completed hourly	Light (normal breathing rate – can sing or talk)

Abbreviations: *AT* Aerobic training, *Ex* Exercise, *RPE* Rating of perceived exertion, *RT* Resistance training

#### Phase 1 (inpatient phase, ~4 weeks)

The individualised, structured, exercise training program delivered during allo-SCT, and acute inpatient recovery will consist of three, 30–45 min sessions of supervised, combined aerobic and resistance exercise per week. Each participant will receive their own stationary exercise bike and set of therabands. Sessions will be conducted within the patient’s room on the hematology oncology ward of the Alfred Hospital, and under the supervision of a physiotherapist, or exercise physiologist.

##### Structured aerobic exercise training

The structured aerobic component of the program will comprise both continuous moderate-intensity exercise and high-intensity interval-based exercise training. Interval training sessions will be performed on an upright cycle ergometer (placed within the patient’s hospital room), while continuous sessions will be performed on an upright cycle ergometer or, when warranted, as a walk around the hematology oncology ward. Continuous moderate-intensity aerobic exercise will be completed twice-weekly, for 20 min, at a workload and/or heart rate corresponding to ~ 60% VO_2_peak or rating of perceived exertion (RPE) 12–14 on the 20-point RPE scale. High-intensity interval training will be completed once weekly (except for the week following stem cell transplantation) and consist of 4 × 2 min intervals at a workload corresponding to ≥ 80% VO_2_peak, 85–95% HR_peak_ and/or RPE ≥ 17, interspersed with 3 min of light intensity cycling for active recovery. All sessions will include a 3–5 min aerobic warm-up and cool-down. Subjective and objective exercise intensity will be monitored using Borg’s 6–20-point RPE scale and participant’s Fitbit heart rate monitor, respectively, and used to adjust exercise workloads to account for the undulating health status inherent in patients undergoing allo-SCT.

##### Structured resistance exercise training

The progressive resistance training component will be completed immediately following the aerobic component and comprise 4–6 compound, body weight and resistance band style exercises with the goal of maintaining muscle strength and mass. The moderate intensity resistance exercise program will include 2 lower body exercises (e.g., squats, lunges, glute bridge, step-ups) and 2 to 4 upper body exercises incorporating both pulling (e.g., resistance band rows) and pushing (e.g., incline push-ups, resistance band chest press) actions to address all major muscle groups of the body. Participants will perform each exercise for 1 set of 15 repetitions at 14–16 RPE and in a slow, controlled manner. The resistance will be increased, or exercise progressed, once 15 repetitions can be completed at ≤ 13 RPE.

##### Sedentary time reduction

Alongside and independent of the thrice-weekly exercise program, participants will receive 10 daily prompts (at hourly intervals) via their Fitbit smartwatch to interrupt their sedentary time with ≥ 3 min of light intensity exercise with the overall objective of reducing total sedentary time by ≥ 30 min/day. When prompted, participants will have the option to break up their sedentary time with ≥ 3 min of light walking, light cycling, or with a simple body-weight resistance exercise circuit comprising squats, calf raises and gluteal kickbacks (each exercise performed for 20 s each, repeated 3 times). When limited to bed rest, participants will be instructed to modify the body-weight resistance exercise circuit to be completed in a supine position in bed. Participants will utilise the exercise tracking feature on their Fitbit to record each sedentary behaviour break.

#### Phase 2 (outpatient phase, 12 weeks)

In phase 2, the individualised exercise program will continue, but with an increase in training volume to 45–60 min per session, and a reduced frequency of in-person supervision to twice per week. Two supervised exercise sessions will be conducted at the BHDI and comprise both an aerobic and resistance training component. The third session will be unsupervised, be aerobic in nature and conducted at each participant’s home. The outpatient program is designed to facilitate a progressive increase in exercise volume of 5–10% each week in line with American College of Sports Medicine (ACSM) guidelines [61].

##### Structured aerobic exercise training

During phase 2, participants will continue to complete one high-intensity interval (supervised) and two continuous moderate-intensity based aerobic exercise sessions per week (one supervised, one unsupervised), but with a progressive increase in volume over the 12 weeks. As per phase 2, continuous moderate-intensity sessions will be performed at a workload and/or heart rate corresponding to ~ 60% VO_2_peak and/or RPE 12–14, beginning at 20 min in week one but progressing one minute each week until participants are completing a total of 30 min in week 12. Intervals will be performed at a workload corresponding to ≥ VO_2_peak, 85–95%HR_peak_ and/or RPE ≥ 17, beginning with 4 × 2 min intervals, interspersed with 3 min active recovery, but gradually progressing to 6 × 3 min intervals, interspersed with 2 min of active recovery. Supervised interval and aerobic training will be performed on an upright cycle ergometer or treadmill, while the unsupervised home-based continuous session will be completed in a mode of the participant’s choice (walking or cycling).

##### Structured resistance exercise training

During phase 2, progressive resistance training will be completed twice weekly, with an increase in total volume and intensity from phase 1. Participants will complete six to eight compound, body-weight, free weight and/or machine-based exercises (3–4 lower body, 3–4 upper body) with the goal of increasing whole body muscle strength and mass. Example exercises include leg press, squats, deadlifts, lunges, and step-ups for lower body, and latissimus dorsi pull-down, seated horizontal row, chest press, and overhead press for upper body. Each exercise will be performed for 2 sets of 10–15 repetitions at RPE 14–16 with 1–2 min rest in between each set. Progressive overload will be applied via periodised augmentation of repetitions and resistance. Specifically, repetitions will be increased by 1–2 each week until participants can exceed the upper end of the desired repetition range (e.g., 15 repetitions), or perform the prescribed repetitions at RPE ≤ 13, after which, the resistance will be increased by 5–10% and participants will resume at a lower repetition goal before progressively increasing again.

##### Sedentary time reduction program

As per phase 1, participants will continue to interrupt their sitting time with 10 daily, hourly light activity exercise breaks.

### Safety precautions: relative and absolute contraindications

Individuals undergoing allo-SCT experience varying degrees of pancytopenia and a range of complications including, but not limited to, loss of appetite, nausea, infections, GVHD, and hemodynamic instability. The prescription of the pre-stated exercise intervention will therefore be individually modified in accordance with patient health status in consultation with the treating hematologist. Absolute contraindications to exercise will include febrility (body temperature > 38 °C), severe pain, nausea and dizziness, platelet count < 15 × 10^9^/L, hemoglobin count < 75 g/L, resting systolic blood pressure > 200 mmHg or < 90 mmHg, resting diastolic blood pressure > 110 mmHg or < 60 mmHg, or resting heart rate > 120 beats/min. Relative contraindications to exercise will include platelet count ≥ 15 × 10^9^/L but < 20 × 10^9^/L, hemoglobin count ≥ 75 g/L but < 80 g/L, resting systolic blood pressure 160–200 mmHg or 90–100 mmHg, resting diastolic blood pressure 90–110 mmHg and resting heart rate 100–120 beats/min. In the instance of a relative contraindication, the prescribed exercise intensity will be limited to light-to-moderate, and signs and symptoms of tachycardia, hypotension and/or hypertension will be closely monitored. Under all circumstances, if a patient becomes symptomatic during activity (e.g., pain, dizziness, nausea), the exercise session will be ceased.

### Usual care control group

Participants randomised to usual care will receive usual medical care throughout the trial. Usual care participants will be fitted with wrist-worn Fitbit activity trackers which will be connected to the cloud-based data aggregation platform (Fitabase Small Steps Labs, LLC, San Diego, CA) to measure day-to-day activity but will not receive exercise support. Additionally, to maintain study engagement, to reduce social-interaction mediated bias on quality of life and mood outcomes, and for equipoise, the study coordinator will visit usual care participants in their hospital room (Phase 1—Inpatient) and at the hematological oncology centre (Phase 2—Outpatient) on a twice weekly basis.

### Experimental protocol

The experimental measures, and their timing are summarised in Table 3. In accordance with the intention-to-treat approach, where possible, experimental testing will be conducted for all participants who deviate from, do not adhere to, or cease participation in the intervention.

**Table 3 Tab3:** Summary of experimental measures and timing of assessment

	**Assessment** **Method**	**Baseline**	**Post-Inpatient**	**12 Weeks Post-Inpatient**
**Primary Outcomes**				
-VO_2_peak	CPET	✔		✔
-Peak cardiac output	ExCMR	✔		✔
**Secondary Outcomes**				
-Quality of life	FACT-BMT	✔	✔	✔
-Fatigue	FACIT-Fatigue	✔	✔	✔
-Functional independence	CPET	✔		✔
**Exploratory Outcomes**				
-Vascular function	CMR	✔		✔
-Cardiac mass	CMR	✔		✔
-Diffuse myocardial fibrosis	CMR	✔		✔
-Diastolic and systolic cardiac function	Echocardiography	✔	✔	✔
-Thigh muscle volume	Thigh MRI	✔		✔
-Thigh muscle fat fraction	Thigh MRI	✔		✔
-Oxygen uptake kinetics	CPET	✔		✔
-Body composition	DXA	✔	✔	✔
-Cardiovascular biomarkers	Blood Samples	✔	✔	✔
-Engraftment indices	Blood Samples	✔	✔	✔
-Development of acute GVHD	Blood Samples	✔	✔	✔
-Anxiety and depression	HADS	✔	✔	✔
-Dietary intake	Diet Diary	✔	✔	✔
-Habitual Physical Activity	Accelerometry/Fitabase	✔	✔	✔
-Habitual Sedentary Time	Inclinometry/Fitabase	✔	✔	✔
-Habitual Sleep Quality	Sleep Log/Fitabase	✔	✔	✔

Cardiopulmonary exercise test (*CPET*), cardiac magnetic resonance imaging (*CMR*), exercise cardiac magnetic resonance imaging (ExCMR), functional assessment of cancer therapy with bone marrow transplant (*FACT-BMT*) questionnaire, functional assessment of chronic illness therapy (*FACIT-fatigue*) questionnaire, dual energy x-ray absorptiometry (*DXA*), graft versus host disease (*GVHD*), Hospital anxiety and depression scale (*HADS*), cardiovascular disease biomarkers include HbA1c, fasting glucose, troponin-I, BNP, LDL- and HDL-cholesterol, triglycerides

The primary outcomes for assessing the efficacy of the intervention on cardiovascular health will be change in VO_2_peak assessed via cardiopulmonary exercise testing and peak cardiac output assessed via exercise cardiac magnetic resonance imaging (ExCMR) (multiple primary outcomes). Secondary outcomes will include prevalence of functional independence (VO_2_peak ≥ 18 mL.kg^−1^.min^−1^) as well as patient reported fatigue and quality of life. Exploratory outcome measures will include changes in cardiac reserve, indices of resting cardiac structure and function (cardiac mass, myocardial fibrosis, diastolic and systolic function), central vascular compliance, cardiovascular biomarkers (troponin-I [cTn-I], brain natriuretic peptide [BNP], glycaemic control, lipid profile and adiposity), skeletal muscle structure and function (lean body mass, thigh muscle cross-sectional area and fat fraction, oxygen uptake kinetics, and muscular strength, power and stability) as well as anxiety, depression and transplant related outcomes including engraftment indices (time to neutrophil and platelet engraftment, immune reconstitution) and development of GVHD. The study will also assess habitual physical activity and dietary intake due to their potential impact on cardiovascular outcome measures. An overview of the protocol assessments and outcomes can be seen in Fig. 2.

**Fig. 2 Fig2:**
[figure not shown]
Overview of protocol assessments and outcomes. LVEF—left ventricular ejection fraction, GLS—global longitudinal strain, cTn-I – troponin-I, BNP – brain natriuretic peptide. Original figure – individual image components sourced from testing at our laboratory

### Cardiopulmonary fitness

Cardiopulmonary exercise testing (CPET) will be used to assess cardiorespiratory fitness (VO_2_peak). This will be performed on an electronically braked cycle ergometer (Lode Excalibur Sport, Lode BV Medical Technology, Groningen, NL) with breath-by-breath expired gas analysis (Vyntus™ CPX, CareFusion, San Diego, CA). Heart rate, rhythm and blood oxygen saturation will be monitored continuously with a 12-lead ECG (Vyntus CPX, Care Fusion, San Diego, CA) and ear clip pulse oximeter, respectively. Brachial blood pressure will be measured at 2 min intervals (Tango M2 ECG-gated automated blood pressure monitor, SunTech Medical Inc., Morrisville, NC). Two minutes of resting data will be collected prior to commencing exercise, following which, an unloaded steady state exercise test will be conducted to assess skeletal muscle oxygen kinetics [62]. Following the unloaded cycling (~ 3–5 min) participants will commence a continuous ramp protocol (5–25 W/min), individualised to participant’s age, weight, and self-reported physical activity levels. Blood lactate concentrations will be assessed at rest, when respiratory exchange rate = 1 (RER1), peak exercise, and 2 min post-exercise via finger prick blood sample (Lactate Pro2, Arkray, Japan). Two minutes of recovery data will be collected following CPET completion to assess recovery oxygen kinetics. Standard criteria will be applied for the assessment of achieving VO_2_peak including the attainment of at least two of the following: volitional fatigue, > 85% age predicted heart rate maximum, RER > 1.1, or blood lactate concentration > 8.0 mmol/L [63]. VO_2_peak will be defined as the average of the six consecutive highest 5 s VO_2_ values, with functional independence classified as VO_2_peak ≥ 18 mL.kg^−1^.min^−1^. Ventilatory threshold (VT) will be assessed using the V-slope method, and the relative proportion of VO_2_peak at which the VT occurs will be used as a measure of changes in submaximal exercise capacity. Ventilatory efficiency (V_E_/VCO_2_ slope) will be obtained via linear regression analysis of minute ventilation (V_E_) and expired carbon dioxide (VCO_2_) from the end of the warm-up to the VT.

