## Background

Since its inception in 1957, allogeneic stem cell transplantation (allo-SCT) has developed from being an experimental procedure to being the best chance of cure for many high-risk hematological malignancies. Accordingly, the last decade has seen a ~ two-fold increase in the number of allo-SCTs performed globally, and the 5-year overall and progression free survival rates are approaching 62% and 52%, respectively, up from 46% and 42% during 1980–1989 [1, 2]. However, the quality and longevity of survival continues to be compromised by treatment-related cardiovascular adverse effects [3]. Owing to the synergistic effects of toxic anti-cancer therapies [4], prolonged bedrest [5], and the inflammatory perturbations of allografting [6, 7], allo-SCT survivors are susceptible to multi-organ impairment. This has resulted in a population characterised by fatigue [8], poor quality of life [9], reduced muscular strength [10], low aerobic capacity (peak oxygen uptake [VO_2_peak]) [11, 12], and an associated 2-to-fourfold elevation in cardiovascular morbidity and mortality [6, 13–18]. Indeed, in a period of 4–12 weeks (inpatient stay and acute outpatient recovery), allo-SCT recipients experience declines in VO_2_peak approximating the degree of cardiovascular aging typically expected over 2–3 decades [11, 12]. Moreover, as many as 53% of allo-SCT survivors meet criteria for functional disability (VO_2_peak < 18 ml.kg^−1^.min^−1^) [12, 19]—a clinical threshold associated with poorer quality of life and a 7-to-ninefold increased risk of heart failure and all-cause mortality [12, 20]. As such, there is growing interest in therapeutic strategies to reduce cardiovascular risk and improve quality of life in allo-SCT survivors.

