Beyond the promotion of purposeful exercise, the reduction and interruption of prolonged periods of time spent sitting or reclining has emerged as an important health target. This is based on the evidence that time spent sedentary poses risks to cardiovascular health that are additional to those of lack of physical activity [43–45]. In the context of allo-SCT, the necessary confinement to a hospital room (~ 3–5 weeks) generally coincides with a marked increase in what is considered an extreme form of sedentary behaviour—bedrest. Thus, a multi-faceted intervention that aims to both increase purposeful exercise and interrupt prolonged periods of sedentary time through replacement with light exercise might be the ideal therapeutic tool to counteract the negative cardiovascular consequences associated with physical deconditioning, cancer therapies, and the pathological perturbations of allografting. Indeed, evidence suggests that structured aerobic and resistance exercise, combined with a reduction in sedentary time, has the potential to have widespread effects on important cardiovascular organs including the heart [46–49], skeletal muscle [50–54], vasculature [47, 55, 56], and blood cells [49], as well as exerting systemic effects that favourably impact these organs [52, 57–60]. No studies have investigated the efficacy of a multi-faceted exercise intervention in preserving cardiovascular function, improving quality of life, and reducing symptoms of fatigue in patients undergoing allo-SCT.

Therefore, in a two-arm randomised controlled trial, the ALLO-Active study will evaluate the efficacy of a ~ 4 month multi-faceted exercise intervention—commenced upon admission for allo-SCT—in preserving cardiovascular function (assessed as VO_2_peak and peak exercise cardiac output; primary endpoints) and improving quality of life, fatigue, and functional independence (VO_2_peak ≥ 18 ml.kg^−1^.min^−1^; secondary endpoints) compared to a usual clinical care control. The intervention is designed to increase purposeful aerobic and resistance exercise and reduce sedentary time through replacement with light exercise and we hypothesise that it will:1. Attenuate the decline in VO_2_peak and peak exercise cardiac output as compared with usual care.2. Improve quality of life, reduce symptoms of fatigue, and improve functional independence compared with usual care.

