### Sample size calculation

No prior studies have directly assessed the effect of a structured exercise intervention on changes in VO_2_peak and cardiac output in this patient cohort. As such, we based our sample size calculations on data collected from our group’s previously published work that utilised a similar exercise intervention in women being treated for breast cancer [74], whereby clinically meaningful changes in cardiorespiratory fitness and cardiac function were observed. The present study is powered to detect a minimum between-group difference in VO_2_peak of 10% (SD = 11%, effect size = 0.91) and cardiac output of 9% (SD = 10%, effect size = 0.9) after treatment, assuming a conservative correlation coefficient of *r* = 0.4 between baseline and follow-up testing. To detect this difference 20 completions per group are required (80% power; alpha = 0.025; multiple primary endpoints). To account for withdrawals, mortality associated with disease progression and treatment, and uncertainty related to the COVID-19 pandemic, a total of 60 participants will be recruited (Ex + SED; *n* = 30 and UC; *n* = 30).

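### Ventilatory threshold as a share of VO2peak cannot be read alone as change in submaximal capacity, because its denominator is a primary outcome expected to fall, and to fall less with exercise (minor)

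*Protocol article*

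**What the plan says.** The Cardiopulmonary fitness section of the protocol article derives the threshold from the exercise test: "Ventilatory threshold (VT) will be assessed using the V-slope method". It then gives the threshold its role: "the relative proportion of VO_2_peak at which the VT occurs will be used as a measure of changes in submaximal exercise capacity". The article does not name VO2 or workload at the threshold, in absolute terms, for that role.

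Two statements in the Background describe how the denominator is expected to behave. On its course over the first 4 to 12 weeks: "allo-SCT recipients experience declines in VO_2_peak approximating the degree of cardiovascular aging typically expected over 2–3 decades". On the treatment effect, the first hypothesis is that the intervention will "Attenuate the decline in VO_2_peak and peak exercise cardiac output as compared with usual care". The Sample size calculation section puts a figure on the latter, a "minimum between-group difference in VO_2_peak of 10% (SD = 11%, effect size = 0.91").

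Table 3 lists VO2peak as a primary outcome, tested at baseline and 12 weeks after discharge. Neither Table 3 nor the outcome list that follows it names the ventilatory threshold as a primary, secondary or exploratory outcome.

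**The concern.** A ratio tracks its numerator over time only if its denominator stays put. Here the denominator is expected to change over the study and to change by a different amount in each arm. The same rise in the ratio could come from a threshold that improved against a stable peak, or from a threshold that fell while the peak fell further. These have opposite meanings for the patient.

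The ratio also gives up a practical advantage of the threshold, which can be found without a maximal effort. Once it is divided by the peak, a submaximal peak effort raises the ratio even when VO2 at the threshold is unchanged. The limitations section says that nausea, fatigue and breathlessness are common in these patients, so this is a realistic possibility.

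The stake is interpretive. A reader of the results could take a higher percentage as better preserved submaximal capacity when the absolute threshold has dropped.

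**Working it through.** The plan gives no figure for the threshold, so there is none to reproduce. Its 20 completers per group concern the two primary outcomes and have no bearing on this point. The check is algebra followed by illustrations.

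**Identity.** Let R0 be the baseline ratio, f the fractional fall in VO2peak and g the fractional fall in VO2 at the threshold. Then

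follow-up ratio = R0 × (1 − g) / (1 − f).

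- g < f: the ratio rises, although the threshold has fallen if g > 0.
- g = f: the ratio does not move, however large the loss.
- g > f: the ratio falls, which is the right direction.

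**Between arms.** With equal baselines, usual care has the higher follow-up ratio whenever its (1 − g)/(1 − f) exceeds that of Ex + SED. Suppose g = k × f with the same k in both arms. The derivative of (1 − kf)/(1 − f) with respect to f is (1 − k)/(1 − f)², which is positive for k < 1. The arm with the larger fall in VO2peak then has the higher ratio.

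**Illustration 1 (all values assumed).** Baseline VO2peak is 2.00 L/min and VO2 at the threshold 1.10 L/min, so the ratio is 1.10/2.00 = 55.0%.

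- Usual care, peak −20% and threshold −10%: 0.99/1.60 = 61.9%, up 6.9 points.
- Ex + SED, peak −10% and threshold −5%: 1.045/1.80 = 58.1%, up 3.1 points.

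Both arms appear to improve, and usual care appears better by 3.8 points although its threshold fell twice as much in relative terms.

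**Illustration 2 (range over k).** Assumed baseline: VO2peak 25 and threshold 14 mL/kg/min, so 14/25 = 56%. Assumed falls in VO2peak: 25% in usual care and 15% in Ex + SED. The gap is the plan's 10% design difference, taken here as 10 percentage points.

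| k | Ratio, usual care | Ratio, Ex + SED | Threshold, usual care | Threshold, Ex + SED |
|---|---|---|---|---|
| 0 | 74.7% | 65.9% | 14.0 | 14.0 |
| 0.5 | 65.3% | 60.9% | 12.25 | 12.95 |
| 0.8 | 59.7% | 58.0% | 11.2 | 12.32 |
| 1 | 56.0% | 56.0% | 10.5 | 11.9 |
| 1.2 | 52.3% | 54.0% | 9.8 | 11.48 |

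- k = 0: the threshold is identical in both arms, yet the ratio favours usual care.
- k between 0 and 1: the absolute threshold favours Ex + SED and the ratio favours usual care.
- k = 1: the ratio shows nothing, while the threshold has dropped 25% and 15%.
- k = 1.2: the direction is right.

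Other assumed falls give the same pattern (usual care against Ex + SED):

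- Falls of 20% and 10%: 63.0% against 59.1% at k = 0.5, and 53.2% against 54.8% at k = 1.2.
- Falls of 30% and 20%: 68.0% against 63.0% at k = 0.5, and 51.2% against 53.2% at k = 1.2.

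**The case against.** The case on the other side has real force on four points.

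- **Not a listed outcome.** The hypotheses, exploratory aims, outcome lists and sample size do not mention the threshold. The factors said to underlie change in VO2peak are cardiac, vascular, hematological and skeletal muscle measures. A reader might infer that the primary result or the account of mechanism is compromised. The documents do not support that.
- **Not stated to be the only measure.** The sentence calls the proportion one measure, and the article condenses a fuller protocol. One cannot infer that absolute VO2 at the threshold will go unreported. It can be recovered as the ratio times VO2peak, and VO2peak is reported in any case, so a careful reader could spot a rise driven by the denominator.
- **The reversal is conditional.** It needs the threshold to fall by a smaller percentage than the peak. The documents give no threshold values, no expected change in it and no percentage fall in VO2peak at the 12-week visit. A reader might infer that the ratio will point the wrong way. The text supports only that it can.
- **Effort is partly controlled.** The section sets attainment criteria for VO2peak: at least two of volitional fatigue, heart rate, respiratory exchange ratio and lactate. These reduce the effort problem but do not remove it, since volitional fatigue is subjective. They do nothing about a genuine fall in the peak.

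These points limit severity. They leave intact that the article assigns the ratio the role of measuring change, and that the ratio is ambiguous in that role.

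**Conclusion.** The concern holds as a minor point. Read alone, the threshold as a proportion of VO2peak does not show whether submaximal capacity rose or fell, nor which arm kept more of it, because VO2peak is itself expected to change with time and treatment. This follows from the identity and from the protocol's own expectations for VO2peak.

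The size cannot be estimated from the documents. In the assumed scenarios with the threshold falling 0.5 to 0.8 times as much as the peak, the ratio favours the arm that lost more by roughly 2 to 5 points. At equal percentage falls it is blind to the loss, and above that its direction is correct. These figures rest on assumed baselines, assumed falls and a common k in both arms. The primary analysis, the secondary outcomes and the sample size are unaffected.

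**What to change.** Define change in submaximal exercise capacity as change in absolute VO2 at the ventilatory threshold, in L/min with mL/kg/min alongside, and analyse it with the same baseline-adjusted model as the other exercise-test measures. Keep the threshold as a percentage of VO2peak as a descriptive companion, and state that it is not read on its own as a change in capacity.

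The cost is one sentence in the Cardiopulmonary fitness section and the matching line in the analysis plan. VO2 at the threshold must already be known to form the ratio, so no new test, visit or data are needed.
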